## Data management

PLCO_M2012_ risk and COPD assessment data will be entered into a RedCap database via a web-based interface. Other data collected during the invitation, risk assessment, SDM process, COPD assessment, biomarker analysis and qualitative evaluation of participant experiences will be entered into an electronic database at the time of collection and will be hosted in New Zealand at Waitematā District Health Board under university level firewall server protection. Data obtained from the screening CT scan e.g. scan result (normal, nodules, suspicious lesions, incidental findings), required follow up (none, nodule management, referral for investigation and management of suspicious and incidental findings), whether the management and follow up has occurred in a specified timeframe, and the results of the follow up will be stored on the study database. The databases will be housed at Waitematā DHB. All databases and electronic storage files will be stored securely and password protected. Data will be de-identified by use of a study ID for each participant. Access to health information will be restricted to key study personnel. A mechanism will be in place for data re-identification so that participants can be contacted should the need for follow up occur. Consent forms will be stored separately from study data.

### Data sharing and governance

No patient-level data will be shared outside of the research team for this study. A Māori data sovereignty assessment was conducted [54-55], confirming the requirement for Māori data governance. All data in this study will be Māori data and will be governed by the Māori members of the steering group, led by the Principal Investigator, with appropriate protections, data access agreements and management procedures consistent with Te Mana Rauranga (the Māori Data Sovereignty Network) principles

### Data and safety monitoring

Data will be monitored daily by the research nurse and research coordinator.

A person independent to the trial will be appointed to monitor the trial conduct. The trial will be monitored after 200 participants have been enrolled, at trial close-out and twice during the trial.

## Ethical considerations

### Informed consent

Informed consent will be sought from all practices and participants involved in the trial. PHOs will provide agreement and clinical approval to join the study. Practices will choose to participate in the study and agree to conduct the study procedures including training, result management and risk assessment (for primary care arm). Consent for participation will be taken by a suitably trained clinician or researcher who is familiar with the risks and benefits of the process.

Consent from participants will use a two-step process; verbal consent to participate in the trial will be sought from people on the list of people who are potentially eligible for the trial and for risk assessment. Eligible participants who decide to undergo a CT scan will be asked to provide written consent for the scan prior to undergoing it. Those who undergo COPD assessment will provide separate written consent. At the same time, separate consent will be sought for a member of the research team to contact the person’s GP to collect data about what actions the GP clinic has taken after receiving the result (patient notification), and to collect data about follow up CT scans, and diagnostic procedures done following the screening CT scan (GP and hospital records).

For the COPD sub-study, explicit consent will be sought to access data collected as part of the main LCS study that are relevant for this study: demographic data (age, gender, ethnicity), co-morbid conditions and smoking data (current smoking status, smoking history including duration and intensity of smoking). Explicit consent will also be sought to access both primary care records and hospital records for the following information: Documentation of COPD and COPD-related diagnoses (emphysema, asthma, chronic bronchitis, bronchiectasis); previous spirometry results; primary care management of COPD including non-pharmacological management and prescribing of medications for COPD and/or related diagnoses (short and long acting anti-muscarinic agents, short and long acting beta agonists, inhaled corticosteroids, oral glucocorticoids, and antibiotics for respiratory symptoms) in the previous 12 months; and the number of acute exacerbation of COPD, GP consults for respiratory symptoms, ED visits or hospitalisations for COPD/respiratory conditions in the last 12 months.

### Other ethical issues

- Possible distress for potentially eligible participants who do not meet risk threshold.
- Possible distress due to discussion of lung cancer or COPD.
- Risk of stigmatisation of smokers and ex-smokers – all people who interact with participants and whānau will be trained in mana-enhancing and mindful engagement to reduce stigmatisation.
- Clear processes needed for managing distress and training for all research team members.

### Adverse events and risks

There is a potential but unlikely risk of a participant suffering an adverse event as a result of participation in this study.

From overseas studies, we anticipate a 1.7% false positive rate when analysing scan results, which means that we anticipate that between 9 and 10 participants will need repeat scans and potentially other more invasive tests before they are given a result of no lung cancer detected. In addition, we anticipate approximately 108 participants that do not have lung cancer will nevertheless have an “indeterminate” scan and require repeat scanning or follow up.

Participants that are referred for further follow up as a result of their screening CT scan will be referred into the standard DHB treatment pathway and will be the responsibility of the treating secondary care physician. We will continue to collect data on outcomes for these participants as part of the study.

De-identified information on all participants referred for follow up will be shared with the study Steering Group. Other potential adverse events and risks of the study are listed below:

**False sense of security:** People who do not meet the risk threshold (so do not receive a scan) and those who have normal scans may incorrectly believe they are not at future risk of lung cancer. Participants will be made aware that being low risk or having a normal CT scan does not exclude future cancers and will be given information about lung cancer symptoms and what actions to take if they develop these symptoms in the future. They may be re-invited to screening in a future screening programme or research follow up study. There is also a small risk of a false negative result. All participants will be advised to see a doctor if they have symptoms of lung cancer in the future, even if their screen is negative.

Exposure to radiation: The radiation from low-dose CT scans is about 14 times that of an x-ray, and delivers about half of the radiation exposure that an average person would usually receive in a year. Having more than one CT scan may slightly increase a participant’s risk of cancer, however, at the relatively low doses of radiation used, the risk of developing cancer from a CT scan is so small that it is difficult to measure it. Participants will be made aware of this small risk

Further testing: If the CT scan identified nodules in the lungs, participants will be offered further tests. The investigation of positive screening scans using diagnostic assessment such as bronchoscopy may be associated with physical harm to participants. In addition, an abnormal result from a CT scan may cause anxiety whilst participants go through this process.

Over-diagnosis: Some small cancers may never have become a problem had they not been diagnosed through screening. Although the extent to which lung cancer LC is over-diagnosed by CT screening is contentious and currently unknown at an individual level, participants will be made aware of this risk.

Information about all these potential risks, and the potential benefits of participating in the study will be provided to participants during the informed consent and shared decision making processes. If whānau do not participate in invitation, risk assessment and shared decision making processes, participants will, if they wish to, be supported to consult with whānau and/or their healthcare providers prior to coming to a decision.

Confirming if follow-up is appropriate may involve a referral to a suitable health professional or specialist. Suitable counselling (clinical, genetic or emotional) may be necessary for participants, depending on the information uncovered. This will be assessed on a case by case basis by the study respiratory physician.

Ethical approval will be sought from the NZ HDEC ethics committee, and any substantial amendments or protocol deviations will be submitted to the approving committee for review.

## Outcomes and Significance

### Primary outcome

To determine the effectiveness of two invitation strategies: primary care vs central hub.

### Secondary outcomes

Secondary outcomes include:

**Eligibility for risk assessment:** Proportion identified as potentially eligible by PHO list who were eligible for risk assessment.

**Completion of Risk assessment:** Proportion of participants who were eligible for risk assessment that completed the risk assessment process. Also an assessment of the differences between the primary care and central hub groups.

**CT scan eligibility:** Proportion of those who underwent risk assessment that met risk threshold for a CT scan by PLCO_M2012_ and criteria-based eligibility.

**Effectiveness of engagement in shared decision making:** proportion of eligible participants that decide to proceed with screening after participating in a shared decision making process to discuss the risks and benefits.

**LCS screening uptake among those eligible:** proportion of those that agree to lung cancer screening who attended and underwent the scan.

- Participant and provider experience of LCS
- Experience and acceptability of the shared decision making and results management processes
- Participant burden using the tools outlined in the study methods
- Provider burden using the processes outlined in the GP clinic based arm of the study
  - The burden on staff and participants will be measured through follow-up interviews and/or focus groups conducted by a member of the research team following the implementation of the pilot.
- Provision of a description of LCS outcomes. This will include The positivity rate of CT scans; the proportion of scans with incidental findings; proportions who proceed to nodule management (interval scans); diagnostic investigations; incidental finding management; the number, stage and types of cancers; response to brief advice to quit; and smoking cessation medications provided and referrals made.
- Assessment of the accuracy of recording of smoking history in general practice

**Prevalence of COPD among those eligible for LCS:** proportion of those eligible who have a spirometry-based COPD diagnosis.

**Change in GP management following provision of results**

**COPD assessment process:**

- Participant and whānau experience of COPD assessment
  - Positive and negative experiences
  - Barriers and facilitators to participation
- Impact of being told the results of assessment
- Participant and whānau views on whether COPD assessment should be included in a future LCS programme, including suggestions for changes to the COPD assessment process.

**Biomarker study**

- Participant and whānau experience of biomarker assessment
  - Positive and negative experiences
  - Barriers and facilitators to participation
- Impact of being told the results of assessment (if applicable)
- Participant and whānau views on whether biomarker assessment should be included in a future LCS programme, including suggestions for changes to the process.

## Appendices

Appendix 1: Lung cancer screening study information booklet

Appendix 2: PIS Risk Assessment

Appendix 3: PIS CT Scan

Appendix 4: Aid for Shared Decision Making

Appendix 5: PIS for clinical staff for interviews / focus groups

Appendix 6: PLCOm2012 Risk Assessment Model

Appendix 7: Script for consent to Shared Decision Making

Appendix 8: Survey after a Risk Assessment – for participants found not to have a high risk of lung cancer (and therefore ineligible for a CT scan)

Appendix 9: Survey about Risk Assessment and Shared Decision Making (for those that decline a CT scan)

Appendix 10: Survey about Shared Decision Making and CT scan (for all participants having a CT scan)

Appendix 11: Survey after a CT scan (selected participants)

Appendix 12: Whānau Tautoko Survey

Appendix 13: Hua Oranga Questionnaire

Appendix 14: Survey after COPD Assessment (all COPD participants)

Appendix 15: Qualitative interview after COPD assessment

Appendix 16: Survey after Biomarker Assessment (all Biomarker participants)

Appendix 17: Pre and post training evaluation form

### Appendix 1: Lung cancer screening study information booklet

###
[figure not shown]

###
[figure not shown]

### Appendix 2: PIS Risk Assessment

See additional attachment

### Appendix 3: PIS CT Scan

See additional attachment

### Appendix 4: Aid for Shared Decision Making

See additional attachment

### Appendix 5: PIS for clinical staff for interviews / focus groups

See additional attachment

### Appendix 6: PLCO_m2012_ Risk Assessment Model

The PLCOm^2012^ risk assessment model will be used to determine risk level for participants that consent to undergo risk assessment.

The PLCO_m2012_ risk assessment model will collect the following information to assess a participants’ risk of developing lung cancer over the next 6 years:

- Age in years
- Education level (less than high school graduate, high school graduate, post high school training, some college, college graduate, postgraduate / professional)
- Body Mass Index (BMI) (weight in kg/height in m^2)
- Does the participant have COPD, emphysema or bronchitis?
- Personal history of cancer
- Family history of lung cancer
- Ethnicity (Māori)
- Smoking status (former smoker or current smoker)
- Average number of cigarettes smoked per day
- Duration smoked
- Years since quitting smoking (if applicable)

In addition to the model parameter, we will also ask participants whether they have worked in jobs for 5 years or more where they have been regularly exposed to any of the following;

-          Asbestos ( e.g. construction, electrical, demolition)?

-          Silica ( e.g. construction, concrete cutting, drilling, working with artificial stone)?

-          Welding fume ( operating arc, stick, MiG, tig, gas as routine part of job)?

-          Have you worked in construction for longer than 5 years in any role?

Furthermore, we also wish to collect information on a person’s passive smoking history. They will be asked the following questions:

The following questions are about your exposure to other people’s smoke, often called “secondhand smoke”

As a child and youth under the age of 18 years, was your exposure to secondhand smoke at home:

🞏 minimal or zero 🞏 Mild 🞏 Moderate 🞏 Heavy

As an adult, was your exposure to secondhand smoke at home:

🞏 minimal or zero 🞏 Mild 🞏 Moderate 🞏 Heavy

As an adult, was your exposure to secondhand at work:

🞏 minimal or zero 🞏 Mild 🞏 Moderate 🞏 Heavy

As an adult, was your exposure to secondhand smoke at private functions: (eg. parties, wedding, meetings,private clubs)

🞏 minimal or zero 🞏 Mild 🞏 Moderate 🞏 Heavy

As an adult, was your exposure to secondhand smoke in public places: (eg. buses, bus stops, bingo halls, bars, clubs)

🞏 minimal or zero 🞏 Mild 🞏 Moderate 🞏 Heavy

### Appendix 8: Survey after a Risk Assessment – for participants found not to have a high risk of lung cancer (and therefore ineligible for a CT scan)

“Survey about your experiences of the lung cancer screening study”

Tēnā koe

As part of our study we are checking your experiences of the Assessment part of the study. Please complete this survey to help us improve the way lung screening is offered in the future. This survey is voluntary.

| 1. Was the study explained to you before your risk assessment? | Yes 🞏 No 🞏 |
| --- | --- |
| 1. Was the information given to you about the study informative and helpful? | Yes 🞏 No 🞏 |
| 1. Was the risk assessment clearly explained to you before it started? |  |
| 1. What would have improved the information you received? (E.g. pictures or diagrams, less jargon) |  |
| 1. What was your first reaction when you were invited to take part in the study? (for example, were you curious/ worried / confused / excited?) |  |
| 1. How did you feel when the Assessment showed you had a normal risk of lung cancer and did not need more screening? |  |
| 1. Do you have any other comments on what worked well or could be improved about this process? |  |
| 1. Were you offered any health related information such as information on smoking?   If not, would you like to be referred to some of our services? | Yes 🞏 No 🞏  Yes 🞏 No 🞏 |

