There are two key strategies for improving stage at diagnosis: earlier diagnosis of symptomatic lung cancer and detection of asymptomatic lung cancer. Earlier diagnosis of symptomatic lung cancer has been demonstrated to produce a small stage shift^15^, but earlier detection of asymptomatic lung cancer is associated with greater stage shift with demonstrated reduction in LC mortality.

The Prostate Lung Colorectal and Ovarian (PLCO_m2012_) model is a lung cancer risk prediction model which has been used and validated by multiple lung cancer screening projects internationally^16^. The PLCO_m2012_ is a logistic regression model based on cancer incidence (over 6 years) that occurred in the Prostate, Lung, Colorectal and Ovarian Cancer Screening Trial (PLCO). This model has higher sensitivity, specificity and positive predictive value when compared to the NLST risk prediction criteria – another internationally recognised criterion which defines a person as of “high risk” when they have a smoking history of ≥30 pack years, have smoked within the past 15 years, and are aged between 55–74. The PLCOm2012 model was developed using U.S. data, and includes variables such as age, education, body mass index, personal history of cancer, family history of lung cancer, COPD, smoking status, tobacco consumption, smoking duration and time since quitting. Race / ethnicity is a significant marker of lung cancer risk. Use of the PLCO_m2012_ risk prediction tool in North America identified that the model under-predicted risk for the American Indian / Alaskan Native and “Black” populations. Ethnicity adjustors were subsequently included in the model. Retrospective studies have demonstrated that selection using model-estimated risk such as the PLCO is superior to NLST-like criteria. Screening using model-estimated risk has higher sensitivity and positive predictive value (PPV), prevents more deaths and has greater cost-effectiveness than screening using NLST-like selection criteria^17^.

In the study described in this protocol, assessment of a person’s risk of developing LC will be undertaken using the PLCO_M2012_ model. On advice from [name] who developed the model we will use a risk threshold of 2.0%; that is, people whose 6-year probability of developing lung cancer is ≥ 2.0% will be offered lung cancer screening. People with a ≥30 pack-years smoking history will be eligible for and offered lung screening even if their risk is below the 2% threshold.

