We have elected to the PLCO_M2012_ model as it has higher sensitivity, specificity, and positive predictive value when compared with the NLST criteria^9^, and has been validated in a number of countries ^18^. It was developed using U.S. data and includes age, education, body mass index, personal history of cancer, family history of LC, chronic obstructive pulmonary disease (COPD), smoking status, tobacco consumption, smoking duration and time since quitting and also includes a predictor for race/ethnic groups as it was found that race/ethnicity predicted LC independently and in addition to the other predictors in the model^19^. In particular, African American and American Indian/Alaska Native (AIAN) populations were at additional elevated risk when compared to Whites and other ethnic groups. It is important to ascertain whether the PLCO_M2012_ accurately predicts Māori risk of LC, and as the model under-estimates AIAN people’s risk of LC, it may also do so for Māori, who are over 3 times more likely to develop LC even though tobacco exposures are similar^6^. We are very interested in assessing how well the PLCO_M2012_ risk prediction model predicts actual prevalence. However, we will not have sufficient power to do this with the sample proposed in this application unless there is a very large difference between predicted and actual prevalence of LC, and this question is the focus of a further proposed study that is currently under assessment by HRC for potential funding. Until we have sufficient NZ data to examine predicted versus actual risk, a conservative approach is required to mitigate the possible underestimation of Māori risk. To this end we will use the ethnicity weighting for AIAN people when calculating risk for the Māori participants.

People with a ≥30 pack-years smoking history will be eligible for lung screening even if their PLCO_M2012_ derived risk is below the 2% threshold. Pack-year is defined as number of packs of cigarettes smoked per day multiplied by the number of years smoked. If a participant stopped smoking for 6 months or more and then restarted smoking again, the time will be subtracted from the total duration of smoking in 0.5-year increments.

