#### Risk Assessment for Prediction of Lung Cancer Risk

The risk assessment will be done by practice nurses (primary care arm) or the project research nurse (central arm) in-person or over the phone depending on patient preference. A standardised protocol for completing the risk assessment will be used; staff in both arms of the trial will receive training in this and a procedure manual will be provided to everyone undertaking these assessments. Whānau or other support people can participate in the risk assessment process.

The PLCO_M2012_ risk prediction tool will be used to assess a participant’s risk of lung cancer. Participants with a $\geq2 \%$ risk of developing lung cancer within six years will be eligible for a CT scan.

People with a ≥30 pack-years smoking history will be eligible for lung screening even if their PLCO_M2012_ derived risk is below the 2% threshold. Pack-year is defined as number of packs of cigarettes smoked per day multiplied by the number of years smoked. If a participant stopped smoking for 6 months or more and then restarted smoking again, the time will be subtracted from the total duration of smoking in 0.5-year increments.

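### Appendix 8 tells people below the scan criteria that the assessment showed a normal risk and no need for more screening, which it does not establish

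*Protocol*

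**What the plan says.** Appendix 8 of the protocol is a voluntary experience survey. Its heading describes the recipients as "for participants found not to have a high risk of lung cancer (and therefore ineligible for a CT scan". One item reads: "How did you feel when the Assessment showed you had a normal risk of lung cancer and did not need more screening".

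The eligibility rule has two routes. Under Background, "people whose 6-year probability of developing lung cancer is ≥ 2.0% will be offered lung cancer screening". Under Risk Assessment for Prediction of Lung Cancer Risk, "People with a ≥30 pack-years smoking history will be eligible for lung screening even if their PLCO_M2012_ derived risk is below the 2% threshold". Never-smokers are excluded (Patient exclusion criteria), and Appendix 6 records only "Smoking status (former smoker or current smoker".

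Adverse events and risks lists a false sense of security as a risk of the study: people below the threshold, and those with normal scans, "may incorrectly believe they are not at future risk of lung cancer". The stated safeguard is: "Participants will be made aware that being low risk or having a normal CT scan does not exclude future cancers". The same paragraph promises information on symptoms and how to act on them, and leaves open a later re-invitation to screening.

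Background accepts that the model has not been shown to be accurate for Māori, and says "a conservative approach is required to mitigate the possible underestimation of Māori risk".

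**The concern.** The item presents an interpretation as the finding of the assessment. The protocol nowhere defines a normal risk of lung cancer. Being ineligible for a scan in this study is also not the same as having no need of one, particularly when the protocol itself says these people may be invited again.

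Two things are at stake. The first is consistency: a study document repeats a reassurance that another section treats as a hazard. The second is the neutrality of the data. Secondary research questions names the questionnaires in Appendices 8 to 17 as sources for the experience outcomes, and Other ethical issues lists possible distress among people who do not meet the threshold. An item that gives a reassuring reading and then asks about feelings is leading on that very topic.

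**Working it through.** **1. What the assessment can show, against what the item says.**

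| Source | Statement about a person who exits at this step |
| --- | --- |
| Eligibility rule (Background; Risk Assessment for Prediction of Lung Cancer Risk) | 6-year model risk under 2% and under 30 pack-years |
| Appendix 8, heading | Not at high risk, so no CT scan |
| Adverse events and risks | Low risk; future cancer not excluded; may be re-invited |
| Appendix 8, item | Risk is normal; no more screening needed |

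The two routes to eligibility are alternatives, so a person exits only by failing both. The first three rows are compatible with each other. The fourth goes beyond them in three ways:

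- *Normal* has no reference group in the protocol, and every recipient is a current or former smoker.
- *Did not need* turns a study cut-off into a statement about the person's need.
- *More* screening suggests that some screening has taken place, although this group has had no scan.

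**2. Comparison with the sister surveys.** Appendices 9 and 10 contain the parallel item for people above the threshold. Those items tie the result to CT eligibility, which the assessment does determine. Appendix 8 could do the same.

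**3. Size of the target group.** Inputs: 4412 invited, 3309 expected to complete risk assessment and 1134 expected to be eligible for LDCT (Synopsis, Expected sample size). From Table 4: completion of 80% and 70% in the two arms, 24% of Māori aged 55-74 eligible for screening, and 70% recorded as not never-smokers.

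The protocol's own figures reproduce:

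- Risk assessments: 4412 × (0.80 + 0.70)/2 = 3309.0, against 3309 stated.
- Eligible for LDCT: 3309 × 0.24/0.70 = 1134.5, against 1134 stated.

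The group not eligible for a scan is 3309 − 1134 = 2175, and 2175/3309 = 65.7%.

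This is an upper limit. The 24% in Table 4 is 28% from smoking history less 4 percentage points for people excluded on other grounds. If those 4 points fall within the 3309, they account for 3309 × 0.04/0.70 = 189 people. That leaves 2175 − 189 = 1986 (60.0%) below the risk criteria. The protocol gives no response rate, so the number who will read or answer the item cannot be derived.

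**4. Below the threshold is not free of risk.** The protocol gives no mean risk for this group. As an assumption for illustration only, take mean 6-year model risks of 0.5%, 1.0% and 1.99% across 2175 people:

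- 2175 × 0.005 = 10.9 lung cancers over six years
- 2175 × 0.01 = 21.8
- 2175 × 0.0199 = 43.3

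The figures depend wholly on the assumed means. They show only why the safeguard exists.

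**The case against.** The strongest reply is that this is one question in a voluntary, retrospective survey and not the notification of the result. Trained nurses carry out the assessment under a standard procedure, and current smokers get cessation advice when it is completed. The Risk Assessment information sheet (Appendix 2) is a separate attachment not seen here and may carry the right message. Normal is not zero, the safeguard paragraph itself uses the term low risk, and re-invitation is only a possibility. All of this stands. It is why the item undercuts the safeguard and does not remove it.

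A reader might infer more than the documents support:

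- *That the survey contradicts the safeguard outright, or that a person just under 2% is told their result is normal.* The survey does not deliver the result, and nothing shows what the nurse says.
- *That this is the last study document such a person sees.* The protocol does not fix when Appendix 8 is given relative to the symptom information.
- *That the trial cannot learn how a below-threshold result is received.* Appendix 8 also has open items, and Secondary research questions adds interviews and focus groups. The item is leading, but it does not decide the experience data alone.
- *That possible underestimation of Māori risk is ignored.* Background applies the American Indian/Alaska Native weighting and adds the pack-year route. Both partly mitigate it, although calibration in Māori remains untested.
- *That 2175 people will read the item.* That figure is the ceiling of the target group.

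What the reply does not answer is that the item states as a finding something the assessment does not establish, and does so before asking for the respondent's reaction.

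**Conclusion.** The point holds as a minor correction. The item attributes to the assessment a conclusion that the eligibility rule, the survey's own heading and the false-reassurance paragraph do not support, and it is leading as a survey question. It reaches at most 2175 people, 66% of those risk-assessed. That rests on the protocol's forecasts of 3309 and 1134 and on everyone found ineligible being offered the survey. The size of any effect on participants' beliefs or on the responses cannot be estimated from the protocol. The primary outcome, randomisation, power and eligibility rules are untouched.

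**What to change.** Reword the item to: *How did you feel when the assessment showed that your risk was below the level at which this study offers a CT scan?* Delete the references to a normal risk and to not needing more screening. The new wording says only what the assessment establishes and brings the item into line with the survey heading and with Adverse events and risks.

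The cost is a minor ethics amendment. Any responses already given to the existing item should be flagged in the analysis file so that they can be told apart from later ones.

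Optionally, add one Yes/No item asking whether the participant was told that lung cancer can still occur and which symptoms to act on. That would make the safeguard checkable, but it is an improvement and not needed to correct the wording.
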